**Figure 1: Study design I**

**Isotope administration:** Iron stable isotope 57Fe (Trace Sciences International) will be converted into an aqueous solution of ferrous sulfate, as described by Ames et al.^25^ Following baseline blood draw and a supervised, 2-hour fast, all enrolled children will receive an oral dose of 57Fe (4 mg)^8^ along with a crushed tablet of vitamin C (50 mg) in 30 mL of fruit juice. Children will be observed for 2 hours after administration of the isotope, and any spilling or vomiting will be recorded. On Day 28, after venous blood draw, an oral dose of 58Fe (1.5 mg) will be given using the identical procedure as for 57Fe. Each 1.5 mg dose of 58Fe will be spiked with 2.5 mg liquid ferrous sulfate to make the total iron content of each dose of 57Fe and 58Fe equivalent. Isotopic enrichment of the blood samples will be calculated by consultant [name], Baylor College of Medicine, as previously described by his research group.^26^These calculations will provide a direct estimate of the proportion of iron isotope incorporated into red blood cells on Day 0 and Day 28. For the purpose of these calculations, each child’s blood volume will be estimated at 80 mL/kg.^26^

**Home visits:** All enrolled children will receive bi-weekly home visits to ensure compliance and to inquire about the overall health of each child. Ill children will be referred to the hospital for care, with transportation provided. Any iron side effects, e.g., constipation, vomiting, diarrhea, will be recorded.

**Sample collection:** *Phlebotomy:* A venous blood sample of no more than 5 mL is routinely drawn from patients with this clinical presentation as part of standard of care. Whole blood will be used for assessment of EP and reticulocytes. This Day 0 blood, along with blood samples drawn at the Day 28 and Day 56 hospital visits will be centrifuged, and plasma collected at the CoreLab located onsite at Mulago Hospital. Plasma will be stored at -80^o^C and then shipped on liquid nitrogen to the University of Minnesota for quantification of iron and inflammatory markers (ferritin, sTfR, hepcidin, CRP, AGP) by immunoassay in the lab of [name]. A finger-prick blood sample will also be drawn on Days 28 and Day 56 for hemoglobin assessment by HemoCue and for Giemsa stain preparation. Red blood cell pellets collected at Day 28 and Day 56 will be re-suspended in saline, stored at -80^o^C, and shipped to Baylor College of Medicine for isotopic analysis by inductively coupled plasma mass spectrometry (ICP-MS) in the laboratory of [name].

*Stool sample:* Per Mulago Hospital guidelines, a stool sample will be collected from each child on Day 0 and analyzed for helminths. Any child found to be infected will be treated with mebendazole.

**Statistical analysis:** For our primary outcome for Aim 1,we will compare Day 0 red cell iron incorporation in the immediate group with Day 28 red cell iron incorporation in the delayed group using a two-sample t-test. Secondary analyses will adjust for baseline characteristics of the children, including age, sex, height, and weight. For our secondary outcome of the association of the change in plasma iron and inflammatory indicators with the change in percentage red cell iron incorporation in each treatment group, strength of trends will be assessed by Spearman correlations. We will also compare the mean change in red cell iron incorporation from Day 0 to Day 28 in the immediate vs. delayed groups using separate multivariate regression models for each indicator. In each model, the change in red cell incorporation will be the outcome variable, and treatment group, Day 0 hemoglobin, and the mean changes from Day 0 to Day 28 in ferritin, sTfR, EP, hepcidin, AGP, or CRP as predictor variables. Models will be further adjusted for sex, age, and anthropometric indices.

**Sample size calculations:** Based on variation between children in 57Fe incorporation reported in Doherty et al.,^8^40 children are needed in each group to provide a clinically significant, detectable difference in red cell incorporation between groups of 4.5%, assuming 80% power and alpha=0.05 (**Table 1**). To account for 20% loss to follow-up, we will recruit 50 children in each group.

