| Outcomes | Aim 1: Primary outcome: Percentage of red cell iron incorporation at the time of initial iron supplement administration (Day 0 incorporation immediate group vs. Day 28 incorporation delayed group)  Secondary outcomes: Association between change in plasma iron and inflammatory indicators (EP, ferritin, sTFR, hepcidin, reticulocytes, CRP, AGP; all continuous) and change in percentage red cell iron incorporation in each treatment group between Day 0 and Day 28.  Aim 2: Primary outcomes: Change in hemoglobin from Day 0 to Day 56 in immediate vs. delayed groups.  **Secondary outcomes:** Change in iron markers (EP, ferritin, sTFR, hepcidin) from Day 0 to Day 56 in immediate vs. delayed groups. |

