The pathophysiology of anemia resulting from co-existing iron deficiency and malaria infection supports this conclusion.The anemia of malaria is complex, with hemolysis of parasitized red blood cells, clearance of both parasitized and non-parasitized red blood cells by reticulo-endothelial macrophages, and impaired bone marrow activity all contributing.^12,13^ Iron that would normally be recycled from degraded red blood cells and transported to the bone marrow for erythropoiesis is instead sequestered in reticulo-endothelial stores under the influence pro-inflammatory cytokines IL-1, IL-6, TNF-α, IFN-γ, the same cytokines implicated in contributing to the alterations in iron metabolism characteristic of the anemia of chronic disease.^14-17^ The antimicrobial hepatic protein hepcidin, an integral regulator of iron metabolism that serves as the soluble messenger among the sites of iron absorption, erythropoiesis, and storage,^18^also plays a key role in these inflammatory changes. Hepcidin concentrations rise during iron sufficiency, down-regulating intestinal iron absorption, and fall during iron deficiency, up-regulating iron absorption. Hepcidin is also a positive acute phase response protein whose concentrations are up-regulated during inflammation under the influence of IL-6^19^--a finding that is thought to explain the alterations of iron metabolism (hypoferremia, hyperferritinemia, anemia) during infectious and non-infectious inflammatory states. Hepcidin acts primarily by binding and degrading the iron-exporting protein ferroportin,^20,21^ blocking iron efflux from intestinal and reticulo-endothelial cells. Multiple studies have confirmed that hepcidin concentrations increase with *P. falciparum* infection^7, 22,23^ and that even mild increases in serum hepcidin can lead to profound disturbances in iron metabolism, including marked hypoferremia, increased serum ferritin, and reduced incorporation of hemoglobin into reticulocytes.^7^

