**Day 0 Procedure:** Children younger than 5 years who present to the Paediatric Assessment Center or Paediatric Acute Care Unit with a positive blood smear will have a finger-prick blood sample for hemoglobin and preparation of Giemsa smear as part of routine care. If hemoglobin is 5.0 – 9.9 g/dL, the Giemsa smear is positive, and the child lives < 50 km from the hospital, the child will be eligible for the study. After informed consent for our research study is obtained (see Informed Consent, below), a venous blood sample will be drawn. Blood samples are routinely drawn on children with this clinical presentation as part of standard of care. After informed consent for our research study is obtained (see Informed Consent, below), drops of whole blood will be dispensed for immediate determination of EP by hematofluorometer (Aviv Biomedical, Lakewood, NJ) and for preparation of a reticulocyte smear. The remaining blood will be sent to Corelab for collection of plasma. Children found to be iron-deficient (EP ≥ 80 µmol/molheme) will be randomized to start 4 weeks of daily iron therapy at baseline, once oral medication can be tolerated (immediate group), or 4 weeks later on Day 28 (delayed group). Any child who is not iron-deficient will not receive iron therapy. Upon enrollment all children will be assigned a randomly generated, unique study identification number that will link clinical forms and samples. Caregivers will be given a clinical follow-up schedule, with dates of bi-weekly home visits and Day 28 and Day 56 hospital visits indicated. On Day 0, participants will be given 2500 USh for transport home. On both the Day 28 and Day 56 visits, participants will receive reimbursement commensurate in value to 15,000 USh. 5000 USh will be given to cover transportation costs to and from the hospital and any cell phone air time needed in the preceding 4 weeks to report illness, and a food package containing oil, rice, and/or sugar valuing 10,000 USh.

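### The announced group comparison of Day 0–28 change in iron incorporation adjusts for a post-randomisation marker change, so it does not estimate the total group difference

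*Protocol*

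**What the plan says.** The Statistical analysis paragraph of the Protocol sets out three layers of analysis for Aim 1.

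- **Primary.** Day 0 incorporation in the immediate group is set against "Day 28 red cell iron incorporation in the delayed group using a two-sample t-test". Secondary versions of this test adjust for baseline characteristics.
- **Association.** Spearman correlations relate marker changes to the change in incorporation within each group. This matches the secondary outcome listed in the Protocol Overview, which concerns the "change in percentage red cell iron incorporation in each treatment group between Day 0 and Day 28".
- **Group comparison of change.** "We will also compare the mean change in red cell iron incorporation from Day 0 to Day 28 in the immediate vs. delayed groups", and this is done "using separate multivariate regression models for each indicator". The specification follows: "In each model, the change in red cell incorporation will be the outcome variable, and treatment group, Day 0 hemoglobin, and the mean changes". The sentence then goes on to name the interval and the markers: "from Day 0 to Day 28 in ferritin, sTfR, EP, hepcidin, AGP, or CRP as predictor variables". Sex, age and anthropometry are then added.

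On treatment, the Day 0 Procedure says that iron-deficient children are "randomized to start 4 weeks of daily iron therapy at baseline, once oral medication can be tolerated (immediate group), or 4 weeks later on Day" (the day meant is Day 28). On mechanism, the Background says: "Hepcidin concentrations rise during iron sufficiency, down-regulating intestinal iron absorption, and fall during iron deficiency, up-regulating iron absorption".

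**The concern.** The stated question is whether the two groups differ in how incorporation changes from Day 0 to Day 28. The stated model answers a different question: whether they differ among children whose ferritin, sTfR, EP, hepcidin, AGP or CRP changed by the same amount. Those changes are measured after randomisation, over four weeks in which one group takes daily iron and the other does not. If iron alters the marker and the marker alters absorption, holding the marker fixed takes that route out of the group coefficient. Conditioning on a post-randomisation variable also opens the coefficient to bias from anything that drives both marker and incorporation, such as an intercurrent infection.

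This contrast is also the only between-group comparison of incorporation over the same calendar period in the protocol, because the primary test compares the groups at different times. A reader of the results would naturally take its group coefficient as the effect of iron timing on incorporation, and would have six of them to choose from.

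**Working it through.** **Order of events.** Randomisation is on Day 0. Daily iron runs from Day 1 in the immediate group only. On Day 28 the venous sample that completes the marker change is drawn before the 58Fe dose is given (Isotope administration). The order is therefore treatment, then marker, then the Day 28 incorporation that enters the outcome. The Background supplies the causal link for hepcidin.

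**What the coefficient estimates.** Let G be the group, M the child's marker change and Y the change in incorporation:

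- M = aG + error
- Y = dG + bM + error

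The total group difference is d + ab. With M in the model and no common cause, the coefficient of G is d. If a share s of the total runs through M, so that s = ab/(d + ab), the adjusted coefficient is (1 − s) × total.

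**Inputs for an illustration.** The protocol states no difference, SD or power for this analysis, so the figures are borrowed from the Aim 1 primary calculation: 4.5 points and 40 per group. Its SD is not stated, but Table 1 implies one (two-sided alpha 0.05 assumed):

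SD = 4.5 × √(40/2) / (1.960 + 0.842) = 7.18

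Across all rows of Table 1 the implied SD is 7.1 to 7.3, so the table is internally consistent. At SD 7.1 the required number is 40 per group, and 40/(1 − 0.2) = 50, as stated. Assumed on top of this: group shifts the marker by 1 SD (a = 1), and the share s varies.

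**Result**, by formula and by simulation (4,000 runs per row, least squares):

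| Share through marker | (1 − s) × 4.5 | Simulated, marker in model | Power, marker in model |
| --- | --- | --- | --- |
| 0% | 4.50 | 4.6 | 72% |
| 25% | 3.38 | 3.4 | 46% |
| 50% | 2.25 | 2.3 | 26% |
| 75% | 1.13 | 1.1 | 11% |
| 100% | 0.00 | 0.0 | 5% |

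Without the marker, every row gives about 4.5 points and about 80% power. In the first row nothing is mediated, and power falls only because group and marker are correlated.

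**Common cause.** Suppose that there is no group effect on incorporation and that the marker has no effect of its own. Let an unmeasured factor correlate 0.5 with the marker within group and contribute 0.4 SD to the outcome (0.4 × 7.1 = 2.84 points). The marker slope is then 0.5 × 2.84 = 1.42, and the group coefficient is 0 − 1.42 × 1 = −1.42. Simulation gave −1.4, with 13% false rejection at a nominal 5%.

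**The case against.** Several points on the other side stand, and they limit the finding.

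- **The randomised comparison is not lost.** A reader might infer that it is. The Aim 1 primary test is unadjusted, its secondary versions use baseline characteristics only, and the Aim 2 comparisons are t-tests with baseline covariates. No post-randomisation marker enters any of them, and the sample size does not rest on the marker models.
- **The adjustment does not remove the whole effect.** The models take one marker each, and each removes only the share running through that marker. Complete removal needs full mediation, which the protocol does not claim.
- **Not all six markers are shown to be mediators.** The Background states the mechanism for hepcidin. It ties CRP to malarial inflammation and its resolution after antimalarial treatment, which both groups receive. Nothing in the document says that iron alters CRP or AGP, or that EP or sTfR governs absorption.
- **The listed secondary outcome is the association, not the group contrast.** For the marker coefficient this model form is reasonable. A reader might add that one common slope defeats an outcome defined within each group, but the Spearman correlations already cover that.
- **The power figures are not the protocol's.** The difference and SD belong to another contrast, and no power is claimed for this one. Nor does the table show a change of sign. That would need opposing pathways or a strong common cause, which the documents do not establish.

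One defence does not stand: that the matter is left to the statistical analysis plan. The protocol names the purpose, the outcome and the predictors, so it has fixed the model, and no marker-free comparison of change appears beside it.

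**Conclusion.** The protocol announces a between-group comparison of the Day 0–28 change in incorporation and specifies only models that cannot estimate its total. Each group coefficient leaves out the part of the effect that passes through its marker, is exposed to common causes of marker and incorporation, and differs across six models. For hepcidin the protocol's own mechanism puts the marker on the pathway. For the other five, the change is post-randomisation, but mediation is not documented.

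The size cannot be fixed from the document, because the share mediated is not given. Under the assumptions above the coefficient falls in proportion to that share, to about half the true difference if half is mediated. This is an illustration, not a forecast for the trial.

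The fault is confined to a secondary contrast. It should be fixed, but it does not threaten either primary analysis.

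**What to change.** In the Statistical analysis paragraph for Aim 1:

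1. State one comparison of the groups on Day 0–28 change in incorporation, from a model with treatment group and Day 0 covariates only (hemoglobin, age, sex, anthropometry).
2. Keep the six marker models, but label them as association analyses. Say that the predictor is each child's own marker change. The present reference to mean changes, read literally as group means, would be collinear with treatment group.
3. State that the group coefficient in the marker models will not be interpreted as the treatment comparison.
4. Optionally, add a group-by-marker-change term and report the within-group slopes alongside the planned Spearman correlations.

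The cost is a few sentences of statistical text. No new data, visits or participants are needed, and the sample size is unchanged.

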**Table 1: Power and sample size for Aim 1**

|  | Detectable difference | |
| --- | --- | --- |
| n per group | Power 80% | Power 90% |
| 30 | 5.2 | 6.0 |
| 33 | 5.0 | 5.8 |
| 40 | 4.5 | 5.2 |
| 43 | 4.3 | 5.0 |
| 50 | 4.0 | 4.6 |
|  |  |  |

For our primary outcome for Aim 2 of the change in hemoglobin from Day 0 to Day 56 in the immediate vs. delayed iron groups, we will compare mean 56-day change (Day 56 minus Day 0) in hemoglobin between the treatment groups using a two-sample t-test. Secondary analyses will adjust for baseline characteristics of children, including age, sex, anthropometric indices, and stool helminth count. For our secondary outcome of changes in iron indicators between Day 0 and Day 58, we will compare the mean 56-day change in each iron indicator (EP, ferritin, sTfR, hepcidin) between treatment groups using a two-sample t-test for each indicator. Secondary analyses will adjust for age, sex, anthropometric indices and helminth count.

**Sample size calculations:** Assuming a SD in the mean change in hemoglobin to be 1.5 g/dL and alpha = 0.05, with 50 children in each treatment group, we would have 90% power to detect a difference of 1.10 g/dL in the mean 56-day change in hemoglobin concentration between groups, assuming 20% loss to follow-up.

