| Study design and procedure | **Day 0**: A venous blood sample is routinely taken from children who present in Acute Care with clinical malaria and anemia (hemoglobin <10 g/dL). Once informed consent is obtained from the caregiver, drops of whole blood will be used to assess erythrocyte protoporphyrin (EP). The EP result will be known immediately. If the child is iron-deficient (EP ≥ 80 µmol/molheme), he or she will be randomized to receive iron before discharge from the hospital (immediate group) or 4 weeks later (delayed group). Iron and inflammatory markers (ferritin, sTfR, hepcidin, reticulocytes, CRP, AGP) will be assessed in each child’s baseline blood sample.  Once consent is obtained and the child is enrolled in the study, each child will be given an oral dose of stable, non-radioactive iron isotope 57Fe mixed with fruit juice,(mango or orange) following a two-hour fast. Caregivers of children in the immediate group will be instructed how to properly administer the first dose of oral iron therapy to be given the following day (Day 1). Iron therapy will consist of a 4-week course of daily ferrous sulfate syrup, based on 2 mg iron/kg body weight.  **Day 28 follow-up visit**: All study children will return to the hospital. A finger prick blood sample will be taken for hemoglobin assessment and for preparation of a Giemsa smear. A venous blood sample will be drawn from all children and sent to Core Lab. Plasma will be collected for assessment of iron and inflammatory markers, and red blood cells will be collected and sent for isotopic analysis. After a two-hour supervised fast, all children will then receive an oral dose of stable, non-radioactive iron isotope 58Fe in an identical manner as on Day 0. Caregivers of children in the delayed iron group will be instructed how to administer the first daily dose of iron syrup to be given the following day (Day 29).  **Day 56 follow-up visit**: On Day 56 all children will return to the hospital for a final finger-prick blood sample (Hb and Giemsa) and venous blood draw (plasma markers plus isotopic analysis) and assessment.  Home monitors will conduct bi-weekly home visits of each child during the 56-day study period to ensure supplement compliance and to assess and record any side effects. Any ill child will be referred to Mulago Hospital and will be provided transportation free of charge. |

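### The Aim 2 primary t-test scores only children seen on Day 56 and leaves the Day 28 hemoglobin unused; loss after Day 28 that depends on recovery differently by group would bias it modestly

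*Protocol*

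**What the plan says.** The Outcomes row of the Protocol Overview gives the Aim 2 primary outcome as "Change in hemoglobin from Day 0 to Day 56 in immediate vs. delayed groups". The Aim 2 analysis text after Table 1 fixes the test: "we will compare mean 56-day change (Day 56 minus Day 0) in hemoglobin between the treatment groups using a two-sample t-test". Secondary analyses of that outcome add baseline characteristics only.

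The Aim 2 sample size text gives the inputs as "Assuming a SD in the mean change in hemoglobin to be 1.5 g/dL and alpha = 0.05", and says that "with 50 children in each treatment group" the trial has enough power: "we would have 90% power to detect a difference of 1.10 g/dL in the mean 56-day change in hemoglobin concentration between groups". It assumes 20% loss to follow-up. The Aim 1 sample size text uses the same allowance: "To account for 20% loss to follow-up, we will recruit 50 children in each group".

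Hemoglobin is measured at the middle visit as well. For Day 28 the Protocol Overview (Study design and procedure) says "A finger prick blood sample will be taken for hemoglobin assessment and for preparation of a Giemsa smear". The Sample collection section says "A finger-prick blood sample will also be drawn on Days 28 and Day 56 for hemoglobin assessment by HemoCue". Day 28 hemoglobin appears in no planned analysis. The Aim 1 regression models use Day 0 hemoglobin only.

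**The concern.** A change score from Day 0 to Day 56 does not exist for a child who misses Day 56, so the named test leaves that child out. A child who attends Day 28 and is then lost has two of three hemoglobin readings and still contributes nothing to Aim 2.

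Day 28 is also where the groups diverge. The immediate group has just finished its four-week course, and the delayed group is told to start the next day. No placebo is described and caregivers give the syrup, so they know the schedule. The reasons for returning on Day 56 could therefore differ by group and be related to recovery so far. If so, the completers are a selected sample, selected differently in each group, and the comparison on Day 56 is shifted. The reading needed to correct much of this is already collected.

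**Working it through.** **1. The plan's own figure.** Inputs from the Aim 2 sample size text: SD 1.5 g/dL, difference 1.10 g/dL, alpha 0.05 (taken as two-sided), 50 per group, 20% loss.

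- Analysed per group: 50 × 0.8 = 40. SE = 1.5 × √(2/40) = 0.335. Normal power = Φ(1.10/0.335 − 1.96) = Φ(1.32) = 90.7%. With the noncentral t, 90.0%.
- With all 50: SE = 1.5 × √(2/50) = 0.300. Normal power 95.6%, noncentral t 95.3%.

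The stated 90% therefore matches an analysis of 40 completers per group.

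**2. Assumptions for the bias.** The protocol gives neither the visit SDs and correlations nor the timing of loss. Assumed: SD 1.2, 1.4 and 1.4 g/dL at Days 0, 28 and 56; correlations 0.45 (Days 0–28), 0.35 (Days 0–56) and 0.6 (Days 28–56); immediate group 0.5 g/dL higher on Day 28; no true Day 56 difference; 20% total loss, of which 15 points fall after Day 28. The implied change SD is √(1.2² + 1.4² − 2 × 0.35 × 1.2 × 1.4) = 1.49, close to the plan's 1.5.

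The correlation between Day 28 hemoglobin and the 56-day change is then (0.6 × 1.4 × 1.4 − 0.45 × 1.2 × 1.4)/(1.4 × 1.49) = 0.420/2.086 = 0.20. Selection on Day 28 hemoglobin therefore reaches the change score only weakly, which keeps the bias modest.

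**3. Simulated bias** (immediate minus delayed, g/dL). Loss after Day 28 is logistic in Day 28 hemoglobin, with the slope given per g/dL. A positive slope means better-recovered children are more likely to be lost.

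| Dependence of loss on Day 28 hemoglobin | Planned t-test | Completers, adjusted for Day 0 | Model using Day 28 |
|---|---|---|---|
| Slope +1 in one group, none in the other | −0.05 | −0.10 | 0.00 |
| Slopes +1 and −1 | −0.10 | −0.22 | 0.00 |
| Slopes +2 and −2 | −0.14 | −0.31 | −0.01 |
| Slope +1 in both groups | about 0 | about 0 | about 0 |

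With random loss there is no bias. Reversing the slopes reverses the sign. Less loss after Day 28 gives less bias. Adjusting completers for Day 0 alone does not cure the problem and can enlarge it, so this is a separate matter from baseline adjustment.

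**4. Precision**, with 40 completers per group under the same assumptions.

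- Planned t-test: 1.49 × √(2/40) = 0.333.
- Day 0-adjusted completers: 1.4 × √(1 − 0.35²) × √(2/40) = 0.293, which is 12% lower.
- Adding Day 28 under random loss lowers this by a further 1–2%.

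**5. How much Day 28 can recover.** Take ρ as the correlation between the Day 28 change and the Day 56 change. The variance of a group mean is SD² × [(1 − ρ²)/n56 + ρ²/n28]. With n56 = 40, all 10 lost children seen on Day 28 (n28 = 50) and ρ = 0.5, the bracket is 0.75/40 + 0.25/50 = 0.02375, an effective 42.1 children per group and 92.0% power against 90.7%. Over ρ from 0.3 to 0.8 the effective number is 40.7 to 45.9 and power is 91.1% to 94.0%. If none of the lost children attended Day 28, the gain is zero.

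**The case against.** **The test is valid and the loss is budgeted.** A pre-specified unadjusted t-test is transparent, and the power figure reproduces. This stands: there is no sample size error here, although a reader might infer one.

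**Missing-data handling belongs in the SAP.** An SAP may exist and was not available. The absence of imputation text is not the point. The protocol names a primary test that cannot score these children and sizes the trial on leaving them out; an SAP that used Day 28 would have to change that test.

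**Loss related to recovery need not bias the comparison.** A reader might infer that the test is unbiased only if loss after Day 28 is unrelated to recovery. That is too strong. Dependence of the same form in both groups largely cancels, as the last row of the table shows.

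**The amount and pattern of loss after Day 28 are conjecture.** This largely stands. The protocol does not time the loss. Aim 1 allows 20% in both groups, although the immediate group's Aim 1 endpoint is read in Day 28 blood, and Aim 2 allows the same 20% at Day 56. Read literally, that leaves no further loss after Day 28 in the immediate group. Home visits and reimbursement are the same in both groups. Against this, 20% is one planning figure used for both aims, not a forecast by visit.

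**Larger biases can be produced.** If all 20% is lost after Day 28, depends on the Day 28 change in opposite directions by group, and ρ is 0.7, the shift reaches 0.37 g/dL. Nothing in the protocol supports that combination.

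**The iron markers.** The Aim 2 marker t-tests have the same form, but no bias has been calculated for them, and Day 28 marker values are used in the Aim 1 models. They should not be described as unused or as shown to be biased.

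**Conclusion.** The point holds as a modest improvement worth making, not as an error that invalidates Aim 2. It is certain from the protocol that the primary test needs a Day 56 value, that the power figure assumes 40 of 50 per group, and that Day 28 hemoglobin is measured but never analysed.

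The bias is conditional. It needs loss after Day 28 that depends on Day 28 hemoglobin differently in the two groups. Under the assumptions shown it is then about 0.05 to 0.15 g/dL, or 5% to 14% of the 1.10 g/dL target (0.05/1.10 and 0.15/1.10). A bias of 0.10 against an SE of 0.33 is a ratio of 0.30, which raises a 5% two-sided error to Φ(−1.66) + Φ(−2.26), about 6%. At 0.15 the ratio is 0.45 and the error is Φ(−1.51) + Φ(−2.41), about 7%.

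A reader might expect Day 28 to buy substantial precision. It does not: most of the gain comes from Day 0, and children lost before Day 28 add almost nothing.

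**What to change.** Make the Aim 2 primary analysis a likelihood-based repeated-measures model of hemoglobin at Days 0, 28 and 56. It should have visit-by-group terms, a common Day 0 mean (or Day 0 as a covariate) and an unstructured covariance, and include all randomised children with usable readings. Keep the Day 56 between-group contrast as the primary estimate, so the Aim 2 question is unchanged. Keep the completer t-test as a sensitivity analysis, and report the number lost before and after Day 28 by group.

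The cost is a sentence or two of analysis text. Visits, samples and the 50 per group stay as they are, and the existing power calculation can stand as a conservative one. The small downside is reliance on missing-at-random given Day 0 and Day 28 hemoglobin; loss that depends on the unseen Day 56 value itself would not be corrected. Using the same model for the Aim 2 markers measured on Day 28 is optional, and its benefit has not been quantified.

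### Aim 2 tests raw hemoglobin change without Day 0 hemoglobin as a covariate: a valid test, but one that may give up precision available at almost no cost

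*Protocol*

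**What the plan says.** The Aim 2 analysis is set out in the text that follows Table 1 of the protocol. For the primary outcome, "we will compare mean 56-day change (Day 56 minus Day 0) in hemoglobin between the treatment groups using a two-sample t-test". No covariate enters that test.

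The adjusted analyses are secondary: "Secondary analyses will adjust for baseline characteristics of children, including age, sex, anthropometric indices, and stool helminth count". Day 0 hemoglobin is not named, though the word *including* leaves the list open. For the iron markers, "we will compare the mean 56-day change in each iron indicator (EP, ferritin, sTfR, hepcidin) between treatment groups using a two-sample t-test". Their adjusted analyses list age, sex, anthropometry and helminth count, and that list is closed. The markers' own Day 0 values are not in it.

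The Aim 1 secondary regressions under Statistical analysis do use baseline hemoglobin. Their predictors are "treatment group, Day 0 hemoglobin, and the mean changes from Day 0 to Day 28" in the plasma indicators.

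The Aim 2 sample-size paragraph works on the change score: "Assuming a SD in the mean change in hemoglobin to be 1.5 g/dL and alpha = 0.05", "with 50 children in each treatment group" and "assuming 20% loss to follow-up", giving the statement "we would have 90% power to detect a difference of 1.10 g/dL in the mean 56-day change in hemoglobin concentration between groups".

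**The concern.** A change score fixes the coefficient on the Day 0 value at exactly 1. A model with Day 0 as a covariate estimates that coefficient. If the true slope of Day 56 on Day 0 is below 1, subtracting the whole Day 0 value adds noise, and the standard error is larger than it needs to be.

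A slope below 1 is plausible here. Day 0 hemoglobin is measured during acute malaria and is limited by eligibility to 5.0-9.9 g/dL, so its link with the value eight weeks later may be modest. Randomization is in blocks of four with no stratification by hemoglobin described, so some chance Day 0 difference between about 40 evaluable children per group is to be expected.

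At stake is the precision of the main clinical comparison. The same reasoning applies to the iron markers, which are also compared as changes without their Day 0 values.

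**Working it through.** **Inputs from the protocol.** SD of 56-day change 1.5 g/dL; alpha 0.05 (sidedness not stated, two-sided assumed); 50 per group with 20% loss, so 50 × 0.8 = 40 evaluable per group; stated power 90% at 1.10 g/dL.

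**Not in the protocol.** The Day 0/Day 56 correlation ρ, the Day 0 SD s0 and the Day 56 SD s1. All three are assumptions below.

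**Step 1: reproduce the stated power.** The standard error is 1.5 × √(2/40) = 0.335. At 1.10 g/dL the noncentral t distribution gives power 90.0% (normal approximation 90.7%). The difference detectable with 90% power is 1.101 g/dL. The protocol's figure reproduces.

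**Step 2: variance with and without adjustment.**

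- Change score: V = s0² + s1² − 2ρ·s0·s1, held at 1.5² = 2.25.
- Day 0 as covariate: s1²(1 − ρ²).
- Share of variance saved: (s0 − ρ·s1)² / V. With s0 = s1 this is (1 − ρ)/2.

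For a fixed sample size the detectable difference scales with the SD, so it becomes 1.101 × √(1 − saving), ignoring the single degree of freedom.

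**Step 3: equal SDs at the two visits.**

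| ρ | Visit SD implied, 1.5/√(2(1−ρ)) | Variance saved | Effective SD | Detectable difference, 90% power |
|---|---|---|---|---|
| 0.2 | 1.19 | 40% | 1.16 | 0.85 g/dL |
| 0.3 | 1.27 | 35% | 1.21 | 0.89 g/dL |
| 0.5 | 1.50 | 25% | 1.30 | 0.95 g/dL |
| 0.7 | 1.94 | 15% | 1.38 | 1.02 g/dL |

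A uniform spread over the eligibility window has SD (9.9 − 5.0)/√12 = 1.41. The rows at 0.5 and 0.7 therefore need a Day 0 spread wider than uniform, so equal SDs are hard to sustain at the higher correlations.

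**Step 4: a smaller SD at Day 0.** Solving V = 2.25 for s1 with s0 = 1.0:

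- ρ = 0.2: s1 = 1.34; saving (1.0 − 0.2 × 1.34)²/2.25 = 24%; detectable difference 1.101 × √0.76 = 0.96 g/dL.
- ρ = 0.5: s1 = 1.72; saving (1.0 − 0.5 × 1.72)²/2.25, about 1%; detectable difference 1.10 g/dL, unchanged to two decimals.

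With s0 = 1.2 the savings at ρ = 0.2 and 0.5 are 41% and 6%. With s0 = 1.41 they are 68% and 17%. The saving is zero when ρ·s1 = s0, that is, when the true slope is 1.

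**Step 5: the price of adjustment.** Residual degrees of freedom fall from 78 to 77. If Day 0 values are roughly normal, estimating the slope inflates the variance on average by 1/(2n − 4) = 1/76, about 1.3%.

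**The case against.** The strongest reply is that nothing here is wrong. Under randomization the t-test on change is unbiased and holds its type I error. It matches the declared outcome, and the sample size is computed on the SD of change and reproduces. Chance imbalance at Day 0 is already reflected in the standard error of the change score. All of that stands.

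A second reply is that the gain is unknown and could be nil. This also stands. Because eligibility truncates Day 0 hemoglobin and not Day 56, a smaller Day 0 SD is a natural expectation. Step 4 shows that the saving can then be about 1%, roughly what the adjustment itself costs.

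A third reply is that Day 0 hemoglobin is itself a baseline characteristic, so the open secondary list could admit it. That is fair for the secondary hemoglobin model, and it would be too strong to say that the plan rules out adjustment everywhere. It does not help the primary test, which is fixed without covariates, or the marker models, whose list is closed.

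Two further inferences are tempting but unsupported:

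- A reader might set 1.10 g/dL against the gain of about 1 g/dL in the Background section and conclude that the trial is sized for too large an effect. That gain was reported among children given concurrent iron and antimalarial therapy. It is not a difference between immediate and delayed iron.
- A reader might infer that the markers will be analysed untransformed. The protocol is silent on transformation, which can be left to the SAP.

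**Conclusion.** The point holds as an improvement at almost no cost. The primary Aim 2 test leaves out a covariate that is already collected and that the protocol itself uses for Aim 1. With 1:1 allocation the adjusted analysis is, in large samples, never less efficient than the change score. At 40 per group its worst case is a loss of about 1% of variance.

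The size is a range that rests on assumptions. With equal visit SDs the saving is 15% to 40% for correlations from 0.7 down to 0.2, and the detectable difference is 1.02 down to 0.85 g/dL against 1.10. With a Day 0 SD of 1.0 it runs from about 24% at correlation 0.2 to about 1% at 0.5. A reader might take one part of this range, such as a quarter to 40%, as an established loss. The protocol does not support that, because it needs correlations of 0.2 to 0.5 together with equal SDs, and neither is given. Nor does the point show bias, an invalid test or an error in the sample size.

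**What to change.** Make the primary Aim 2 analysis a linear model of Day 56 hemoglobin on treatment group with Day 0 hemoglobin as covariate, and report the group coefficient with its confidence interval. Using change as the dependent variable in the same model gives an identical group coefficient, so the declared outcome need not be altered. Keep the mean raw change per group as a descriptive summary.

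Name Day 0 hemoglobin in the adjusted secondary hemoglobin models. Analyse each iron marker (EP, ferritin, sTfR, hepcidin) at Day 56 on group with that marker's own Day 0 value as covariate.

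The sample size can stay as it is, since the stated power becomes a conservative figure if the correlation is modest. The cost is a few sentences of protocol or SAP text, agreed before outcome data are examined, and one residual degree of freedom per model. No extra measurement is needed.
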